***V.1. Visit 1: Screening***

**On Day 1, the research subject will present to the clinical research center after an overnight fast.** He/she will have had the opportunity to read the consent form ahead of time (see below). All questions will be answered, signed informed consent will be obtained and a brief history will be taken in order to verify inclusion and exclusion criteria. During the consenting process, the subjects will be informed on how to fill out a four day food record. On occasion, if it is convenient for the subject, signed informed consent may be obtained prior to Day 1. Women of childbearing age who are currently sexually active and not using birth control will receive a urine pregnancy test. Vital signs and anthropometric measurements (height and weight) will be obtained by a nurse. Eligible and willing subjects will then proceed to the sulfonylurea challenge as part of this initial visit.

[figure not shown]

***V.2. Day 1: Sulfonylurea challenge***

**In order to prevent significant hypoglycemia, a baseline fingerstick >80 mg/dl will be required.**

If the blood glucose is between 70 mg/dL and 80 mg/dL, and the subject has arrived before 8am, *or* the patient is very interested in proceeding with the study, he or she will be offered the opportunity to have a second blood glucose drawn at least 30 mins after the initial check. If the second glucose is above 80 mg/dL, proceed with the standard study protocol. If the subject does not wish to proceed, or if the fasting glucose is below 80 mg/dL, only baseline blood will be drawn. The subject will still be invited to come back for Visit 2 (Day 8).

Subjects will then have a 20G intravenous catheter placed, and baseline (time 0) serum insulin, metabolomic profiling, C peptide and glucose will be obtained. In addition, a comprehensive metabolic panel and an extra 20 cc tube of whole blood for DNA extraction will also be drawn. They will then receive a single oral dose of glipizide 5 mg, and simultaneous insulin and glucose will be obtained at 30, 60, 90, 120, 180 and 240 minutes. Additionally, metabolomic profiling samples will be drawn at 60 and 120 minutes. Routine glucose measurements (for subject safety) will also be obtained every half an hour from intravenous blood. The frequency of blood glucose measurements will increase to every 5 minutes for an asymptomatic glucose <50 mg/dl. If the subject develops symptoms of hypoglycemia (diaphoresis, lightheadedness, confusion, anxiety, new onset of hunger or tiredness) another glucose measurement will be obtained: 1. If glucose > 50 mg/dl, glucose measurements will increase to every 10 minutes. If subject no longer feels symptoms of hypoglycemia, the nurse may return to routine checks after 3 documented rising or stable blood sugars. 2. If any glucose measurement is <50 mg/dl (with symptoms) or 45 mg/dl (without symptoms) or if nurses detect symptoms such as confusion, blurred vision and slurred speech, regardless of glucose measurements, the challenge will be aborted and the patient will be given juice and a glucotab, and advised to break his/her fast immediately. If the subject cannot swallow, 1 amp of D50 will be administered by IV. At the conclusion of the sulfonylurea challenge, every subject will be fed a provided meal rich in carbohydrate content. Any subject with persistent symptoms of hypoglycemia after the full meal will have another glucose measurement; persons with a glucose <80 mg/dl will be monitored for another 3 hours at the clinical research center, or longer if deemed necessary for their safety by the PI.

Before discharge, the patient will receive three 500 mg metformin pills to take home with the appropriate instructions. If subject suffered symptoms of hypoglycemia, the nurse will provide them with an educational pamphlet on monitoring blood sugar as well as a snack to eat at home. Days 1-6 will constitute the washout period for the single administered dose of glipizide (~12 half-lives by a conservative estimation).

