***V.6. Choice of drugs and doses***

**Glipizide** was chosen among sulfonylureas because it has great oral bioavailability, immediate onset (initial response at 30 minutes, peak response at 2-3 hours), relatively short half-life (2-8 hours, 10 hours in the elderly) and no need of adjustment for renal insufficiency or age. The chosen dose (5 mg) is the initial dose commonly used in type 2 diabetes, and represents a reasonable compromise between achieving an effect of sufficient magnitude while avoiding severe hypoglycemia. Severe hypoglycemia requiring assistance occurs 0.19-2.5 episodes per 1000 patient years. **Metformin** is the only drug available in its class, and was chosen to replicate and extend the findings observed in the DPP. We have elected submaximal doses to avoid gastrointestinal side effects and ensure short-term adherence to the protocol. Metformin will not be administered to individuals with renal dysfunction.

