- - 1. **During the sulfonylurea challenge, subjects are expected to become hypoglycemic.** The degree of hypoglycemia may be blunted in our population at risk of diabetes, for whom some amount of insulin resistance is likely to be present. In addition to the exclusion of subjects with impaired renal or hepatic function (in whom duration of action may be more pronounced), we will take the following precautions to avoid complications of severe hypoglycemia: 1) exclusion of subjects with a fasting fingerstick < 80 mg/dl, 2) selection of a low dose of glipizide, 3) close monitoring of subjects for the appearance of hypoglycemic signs and symptoms (diaphoresis, nervousness, jitteriness, shakiness, confusion, blurred vision, lightheadedness, slurred speech), 4) rapid fingerstick measurement if any of the above are noted, 5) half-hourly fingerstick glucose measurements even in the absence of symptoms, 6) increase in the frequency of fingerstick measurements (even when asymptomatic) if these drop below 50 mg/dl, and 7) termination of the challenge with juice and a glucotab if the fingerstick is <50 mg/dl (with symptoms) or <45 mg/dl (without symptoms), with indications that the subject break his/her fast immediately. We will also have IV dextrose on standby, and will provide all subjects with a carbohydrate-rich meal at the conclusion of the challenge. Metformin only causes hypoglycemia when used in combination with other hypoglycemic agents; in order to avoid this eventuality we have established a safe washout period. Even with the conservative estimation of prolonged glipizide half-life in the elderly (~10h), a total of 12 half-lives will have transpired between Day 1 and Day 6, essentially eliminating any chance of both drugs interacting in any subject.

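### Section V.2 expressly orders a post-meal glucose only for persistent symptoms, so a subject whose challenge was aborted without symptoms can leave with no documented glucose recovery

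*Protocol*

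**What the plan says.** Protocol section V.2 ties its checks during the challenge to glucose as well as to symptoms. Safety glucose is taken every 30 minutes. Below 50 mg/dl the schedule tightens: "The frequency of blood glucose measurements will increase to every 5 minutes for an asymptomatic glucose <50 mg/dl". The abort rule has a limb for subjects who feel nothing: "If any glucose measurement is <50 mg/dl (with symptoms) or 45 mg/dl (without symptoms"; certain signs seen by the nurse also end the challenge at any glucose. An aborted subject receives juice and a glucose tablet and is told to eat.

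Section VII.1 repeats the abort rule, with the asymptomatic limb as below 45 mg/dl. Among its precautions it lists "half-hourly fingerstick glucose measurements even in the absence of symptoms" and "increase in the frequency of fingerstick measurements (even when asymptomatic) if these drop below 50 mg/dl".

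Once the challenge is over, V.2 gives every subject a carbohydrate-rich meal and then states: "Any subject with persistent symptoms of hypoglycemia after the full meal will have another glucose measurement". The same sentence goes on: "persons with a glucose <80 mg/dl will be monitored for another 3 hours at the clinical research center", or longer if the investigator judges it necessary. The discharge paragraph sets no glucose condition for leaving. Its one hypoglycemia precaution is again tied to symptoms: "If subject suffered symptoms of hypoglycemia, the nurse will provide them with an educational pamphlet on monitoring blood sugar", together with a snack to take home.

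**The concern.** Section VII.1 puts hypoglycemia first among the risks and says it is expected during the challenge. The protocol plainly recognises that a subject can be low without feeling it, because it sets a separate abort level for that case. For such a subject, absence of symptoms after the meal says little about whether glucose has recovered: symptoms have already failed to signal the low value. A symptom trigger is therefore the wrong one for this group at the point where the decision to let the subject go is made.

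What is at stake is the safety of a small, identifiable group. No endpoint, power statement or analysis is affected.

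**Working it through.** The protocol gives no figure to reproduce. The check is to follow a subject through the text.

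**Step 1. The subject in question.** Glucose reaches the asymptomatic abort level. The challenge stops; juice, glucose tablet, advice to eat and the meal follow. There are no symptoms after the meal, so the only express post-meal order is not triggered.

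**Step 2. What else could apply.** Two points in V.2 are open. The half-hourly and 5-minute checks have no stated end, so they may stop with the challenge or run on. The 80 mg/dl clause names no symptoms, but it follows directly on the symptom-triggered measurement. It may refer to that value only, or to anyone whose last glucose was low. The combinations are:

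| Checks after abort | 80 mg/dl clause | Result for the asymptomatic aborted subject |
| --- | --- | --- |
| Stop | Symptom-triggered value only | No glucose ordered, no observation |
| Stop | Any last low value | Kept 3 hours on the value before rescue; no repeat glucose ordered |
| Run on | Symptom-triggered value only | Values taken until an unstated end; a value below 80 starts no observation |
| Run on | Any last low value | Values taken and observation below 80 |

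Only the fourth combination gives both a repeat glucose and the observation rule. The first two order no glucose after rescue and meal.

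**Step 3. The neighbouring case.** A subject at 45-49 mg/dl without symptoms when sampling ends at 240 minutes has not been aborted under the VII.1 wording and is under the 5-minute rule. If that rule runs until glucose reaches 50, the subject is partly covered. What is left is the stretch from 50 to 80 mg/dl, for which nothing is expressly ordered after the meal.

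**Step 4. A milder case in the same section.** A subject with symptoms but a glucose above 50 mg/dl is checked every 10 minutes. Once the symptoms have gone, routine checks may resume only after three recorded values that are stable or rising. V.2 thus asks for documented recovery there, but not expressly after an asymptomatic abort.

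**Step 5. Other sections.** The rest of VII.1, the monitoring plan (IX.1) and the adverse event rules (IX.2) contain no further requirement for a glucose after rescue or meal.

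**Step 6. Drug action.** Section V.6 gives "peak response at 2-3 hours), relatively short half-life (2-8 hours, 10 hours in the elderly". The challenge lasts 240/60 = 4 hours, so the longer half-lives outlast it. This is a reason not to treat the end of sampling as the end of drug effect. It is not an estimate of glucose after the meal.

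**The case against.** The strongest reply is that the protocol is silent here and does not order monitoring to stop. What is aborted is the challenge; the safety checks carry no end time, and the 5-minute rule makes no exception for an aborted subject. The observation clause speaks of persons with a low glucose and leaves the investigator free to extend the stay. Treatment does not depend on symptoms. The truly asymptomatic group is narrow: a baseline fingerstick above 80 mg/dl is required, the dose is low, the symptom list includes new hunger or tiredness, and signs seen by the nurse also abort the challenge. A nursing order at the research center might already require a recheck; none is in the documents, so this cannot be judged.

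Much of this stands. A reader might infer that the protocol sends subjects home while still hypoglycemic, or that no glucose at all is taken after an asymptomatic abort. The text supports neither: the first ignores rescue and meal, the second depends on one reading of rules that have no stated end. A reader might also try to size the harm from the number of checks during the challenge, from the distance between 45 and 80 mg/dl, or from the drug remaining under the V.6 half-lives. None of these measures glucose after rescue and a meal.

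What does not stand is the suggestion that the wording is therefore adequate. V.2 does state a post-meal rule, and its trigger misses a group that the same section recognises. Whether that subject is rechecked or observed should not rest on how a nurse reads an open clause.

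**Conclusion.** The point holds as a defect in a stated safety rule. The only glucose expressly ordered after the meal depends on persistent symptoms, and the text leaves open whether anything else covers a subject aborted without symptoms. Such a subject can be discharged within the protocol with no documented recovery.

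The size is unknown. The documents do not say how often glucose falls below 50 mg/dl without symptoms, nor how glucose behaves after rescue and meal. The residual risk is reduced by juice, glucose tablet and meal. The conclusion rests on the protocol text alone and assumes that no separate nursing order already closes the gap. It should be fixed because the change is cheap and concerns the risk that the protocol lists first. The difference between 45 and below 45 mg/dl, and the symptom condition on pamphlet and snack, are minor.

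**What to change.** Amend V.2 and align VII.1. Any subject whose challenge was aborted, or who had a glucose below 50 mg/dl, with or without symptoms, has a documented glucose after rescue and meal and before discharge. The existing 80 mg/dl / 3-hour observation rule applies to that value regardless of symptoms.

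In the same edit, state when the 5-minute checks end, use one asymptomatic abort threshold in both sections, and give these subjects the pamphlet and snack.

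The cost is protocol wording, one extra bedside glucose for subjects who met a low-glucose trigger, and a longer stay for a few of them. The added value is taken after the challenge has ended. It should be recorded as a safety measurement and kept out of the Specific Aim 1 glucose endpoints in section VI.1, so no endpoint changes.

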**V.3**. **Days 2-7: Food record**

**The participants will fill out a dietary intake food record.** The food record will span 3 weekdays and one weekend day. They will use a standardized food record provided by the MGH Bionutrition/Metabolic Phenotyping Core. They will be asked to bring this detailed food record to Visit 2.

***V.4. Days 6-7: Short-term metformin treatment***

**The baseline serum creatinine will be used to recalculate GFR.** If the new estimated GFR is < 60 ml/min/1.73 m^2^ based on the MDRD equation, the subject will undergo a simple OGTT on Day 8 in the absence of any metformin treatment. In addition, we will also ensure that for subjects who are taking a diuretic medication, their dose remains stable between Visits 1 and 2; if it doesn’t, the patient will be asked to refrain from taking metformin and will present for a simple OGTT. Likewise, we will check ALT and AST levels from the baseline comprehensive metabolic panel, and if either one is 3x higher than the upper limit of normal the subject will be asked not to take the metformin and instead report for a simple OGTT. Otherwise, he/she will be asked by telephone or email to begin taking the first dose of metformin in the evening of Day 6, and to take the other two doses with breakfast and supper on Day 7. The subject will then be asked to keep another overnight fast.

Should the subject need to reschedule his/her second visit due to an unforeseen circumstance, and he/she took one or more metformin at home, arrangements will be made to supply another course of metformin to him/her before his/her rescheduled second visit.

***V.5. Visit 2: OGTT on metformin***

**On Day 8, the research subject will again present to the clinical research center after an overnight fast.** A baseline fingerstick will be taken and if the fasting blood sugar is <60 mg/dl, the subject will receive the metformin ten minutes after the Glucola administration instead of an hour prior**.** If fasting blood sugar is >250 mg/dl subject will be excluded and study terminated. As long as the fingerstick glucose is >60 mg/dl and <250 mg/dl, the subject will receive the 4^th^ dose of metformin 500 mg, and have a 20G intravenous catheter placed; one hour later a 75g OGTT will commence. Insulin and glucose will be obtained at 0, 30, 60 and 120 minutes, and a separate tube will be frozen for GLP-1 determination at each time point (in addition, GLP-1 tubes will also be obtained at 5, 10 and 15 minutes; leftover serum will be frozen for future metabolomic profiling). Additionally, metabolomic profiling samples will be drawn at 0, 60 and 120 minutes. After the last dose of metformin has been administered, the subject will review his/her food record with an MGH diet technician. If he/she forgets to bring the food record, they will be provided with a stamped envelope to mail a copy of the food record to the study coordinators and the study coordinators will review the food records by phone.

At the conclusion of the OGTT the subject will be dismissed and the study concluded. A schematic version of the protocol for medication administration and blood draws is shown in Fig. 4.

***V.6. Choice of drugs and doses***

**Glipizide** was chosen among sulfonylureas because it has great oral bioavailability, immediate onset (initial response at 30 minutes, peak response at 2-3 hours), relatively short half-life (2-8 hours, 10 hours in the elderly) and no need of adjustment for renal insufficiency or age. The chosen dose (5 mg) is the initial dose commonly used in type 2 diabetes, and represents a reasonable compromise between achieving an effect of sufficient magnitude while avoiding severe hypoglycemia. Severe hypoglycemia requiring assistance occurs 0.19-2.5 episodes per 1000 patient years. **Metformin** is the only drug available in its class, and was chosen to replicate and extend the findings observed in the DPP. We have elected submaximal doses to avoid gastrointestinal side effects and ensure short-term adherence to the protocol. Metformin will not be administered to individuals with renal dysfunction.

***V.7. Subject confidentiality***

**At all moments, the privacy of research subjects will be protected.** Subjects will receive a coded, anonymous numerical identifier that will link their anthropomorphic, biochemical and genetic measurements to each other but not to the individual. The key will be stored in the PI’s office in a locked cabinet and in his password-protected hard drive. A code will also be used to mark his/her self-reported ethnic group. If the OGTT suggests the presence of diabetes in a previously undiagnosed subject, the subject (and his/her primary care physician if agreed beforehand) will be contacted for appropriate follow-up and confirmation.

***V.8. Laboratory procedures***

**V.8.a. Biochemical measurements**

**The local assay laboratory will perform all biochemical measurements of glucose, insulin, C peptide and serum creatinine.** Urine HCG pregnancy tests and fingersticks will be carried out in the clinical research center by the study nurse. Separate tubes for DNA (Visit 1) and GLP-1 (Visit 2) will be frozen and stored in the PI’s laboratory in a -80^o^C freezer. All tubes will be labeled with a coded, anonymous identifier.

**V.8.b. DNA extraction and genotyping**

**DNA will be extracted with a standard DNA isolation kit.** The Puregene alcohol precipitation kit from Gentra systems will be used to extract DNA from 10cc of whole blood (the other 10cc will be kept frozen as a backup), expected to yield 150-300 μg of DNA. DNA will be quantified by Picogreen analysis and plated onto 96-well storage plates, from which 384-well working plates will be prepared. Each plate will have a unique configuration of empty wells so as to be able to detect plate misassignment, and will also include a number of duplicate samples. The gender of each sample will be verified by genotyping the sex-specific AMELXY polymorphism. All tubes will be labeled with a coded, anonymous identifier.

**Genotyping will be performed by allele-specific primer extension of single-plex amplified products, with detection by matrix-assisted laser desorption ionization-time of flight mass spectroscopy on a Sequenom platform (**[**82**](#_ENREF_82)**).** Hardy-Weinberg equilibrium will be tested within each self-described ethnic group, and overall call and consensus rates will be determined. In our hands, this genotyping platform routinely produces call rates >98% and consensus rates >99%. Genotyping activities will take place in collaboration with the Genomics Platform at the Broad Institute, of which the PI is an Associate Member.  Similarly, metabolomic profiling will take place in collaboration with the Metabolite Profiling Platform at the Broad Institute.  Only samples and basic phenotypic data will be shared with investigators at the Broad Institute; all PHI will remain at the MGH site under password-protected electronic files and/or in a locked office.

**V.8.c. GLP-1 measurements**

**GLP-1 will be measured through radioimmunoassays validated in the MGH-based Boston Area Diabetes Endocrinology Research Center (P30) core laboratories.** Due to the relatively short half-life of active GLP-1 (amino acids 7-36) that is cleaved by DPPIV to generate inactive GLP-1 (amino acids 9-36), we plan to measure both total and active GLP-1 levels in our subjects. We will use a specific antibody to the C-terminus of GLP-1 to measure total GLP-1 levels, and a second specific antibody targeting the N-terminus of GLP-1 to measure the active GLP-1 (amino acids 7-36) levels. Laboratory technician [name], who has extensive longitudinal experience in conducting GLP-1 assays, will perform these measurements. For GLP-1 measurements, blood samples will be collected in prechilled tubes containing EDTA, kallikrein-trypsin inhibitor (Trasylol), and diprotin A. GLP-1 radioimmunoassays will be conducted according to established laboratory protocols ([83](#_ENREF_83)).

1. **Data Analysis**

***VI.1. Study endpoints***

**The study will have the following primary endpoints, according to each Specific Aim:**

Specific Aim No. 1 – Sulfonylurea challenge: Trough glucose and peak insulin levels will be compared by genotype. Secondary endpoints will be differences in glucose and insulin areas under the curve (AUC, calculated by the trapezoidal method), as well as glucose and insulin at 2 hours. Leftover serum samples will be frozen for glucagon level measurements.

Specific Aim No. 2 – Acute metformin effect on insulin sensitivity: The insulin sensitivity index (reciprocal of insulin resistance by homeostasis model assessment ([84](#_ENREF_84))) will be calculated as 22.5/[fasting insulin x (fasting glucose/18.01)], and compared by genotype. A secondary endpoint will be differences in the insulinogenic index by genotype after metformin treatment, calculated as [(insulin at 30 min) – (insulin at 0 min)]/[(glucose at 30 min) – (glucose at 0 min)].

Specific Aim No. 3 – insulinogenic index and GLP-1 levels during OGTT: The insulinogenic index, calculated as above, will be compared by genotype, and the differences between genotypic groups will be contrasted to those observed during the sulfonylurea challenge (Specific Aim No. 1). A subset of subjects (selected to have equal numbers in each genotypic group) will have their GLP-1 levels measured, and peak GLP-1 as well as AUC will be compared by genotype. Leftover serum samples will be frozen for metabolomic profiling and glucagon level measurements.

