**I.3.b. Prospective evaluation of associated polymorphisms**

[figure not shown]

P < 0.01

**We have examined these validated associations prospectively**. As part of the second Specific Aim in the PI’s K23 Research Career Development Award, and under the mentorship of [name], we have collaborated with the Diabetes Prevention Program (DPP) in testing whether specific genetic variants predict the development of diabetes in a multi-ethnic population of subjects with IGT and affect their response to preventive interventions. Consistent with prior cross-sectional studies, homozygotes for the proline allele in *PPARG* P12A progressed more rapidly from IGT to diabetes than alanine carriers (HR 1.24, 95% CI 0.99-1.57, *P*=0.07), with no interaction between genotype and intervention. There was a significant interaction of genotype x BMI, with a stronger relationship between BMI and progression to diabetes in alanine carriers. We detected no statistically significant effect of genotype on quantitative glycemic traits at baseline, nor on troglitazone response at one year (Florez *et al.,* in preparation).

Fig. 2: Effects of *KCNJ11* E23K genotype on baseline insulin to glucose ratio (IGR) in the Diabetes Prevention Program.

**The effect of *KCNJ11* E23K on development of diabetes and on related traits was more complex.** As previously reported in normal subjects, lysine carriers at *KCNJ11* E23K had reduced insulin secretion at baseline (Fig. 2). Nevertheless, EK heterozygotes were *less* likely to develop diabetes than EE homozygotes (HR 0.70, 95% CI 0.54-0.91, *P*<0.01), in a direction consistent with a large prospective study ([19](#_ENREF_19)). There was a novel interaction of metformin with E23K genotype (*P*=0.02): lysine carriers displayed a diminished preventive effect of metformin (HR 0.89 [95% CI 0.66-1.19] for EK and 0.95 [95% CI 0.54-1.67] for KK vs placebo), while EE homozygotes had a greater preventive effect (HR 0.55 [95% CI 0.42-0.71]).

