**We therefore propose the following Specific Aims:**

Specific Aim No.1: To examine the acute response to a sulfonylurea challenge (glipizide 5 mg orally) in subjects at risk of diabetes or with early diabetes (on diet treatment alone), depending on genotype at *KCNJ11* E23K, *TCF7L2* rs7903146, or newly discovered variants linked to type 2 diabetes via associations with related phenotypes, individually or in aggregate

- We hypothesize that subjects with a subset of variants will have an attenuated response, whereas those with a different subset will have no discernible impact on this response

Specific Aim No. 2: To examine the acute response to short-term metformin treatment on the insulin sensitivity index in the same group, depending on genotype at *KCNJ11* E23K, or newly discovered variants linked to type 2 diabetes via associations with related phenotypes, individually or in aggregate

- We hypothesize that subjects with a subset of variants will have a diminished improvement in insulin sensitivity compared to non-carriers

Specific Aim No. 3: To examine acute insulin secretion (by the insulinogenic index derived from an OGTT), GLP-1 and glucacon levels, and metabolomic profiling after short-term metformin treatment (500 mg bid x 4 doses) in the same group of subjects, depending on genotype at *TCF7L2* rs7903146, or newly discovered variants linked to type 2 diabetes via associations with related phenotypes, individually or in aggregate

- We hypothesize that subjects with the risk TT genotype at *TCF7L2* rs7903146, or a subset of variants will have a reduced insulinogenic index and GLP-1 levels than non-carriers

***If successful, this proposal should help clarify the pathophysiologic mechanisms by which these key genetic variants increase risk of type 2 diabetes, and assess their impact on commonly used antidiabetic treatments. In addition, this pilot study will lay the groundwork for a long-term, outcomes-based pharmacogenetic clinical trial.***

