***VI.2. Statistical analysis***

**Non-normal variables will be log transformed.** They will be adjusted for age, gender and BMI, and residuals will be compared between each group of homozygous individuals at each locus by Student t tests. Since these polymorphisms may influence glycemic traits by affecting BMI, both BMI-adjusted and unadjusted analyses will be reported. Secondary analyses will include exploration of genetic models (dominant, recessive or additive), by including heterozygous individuals and performing ANOVA across the three genotypic groups, with subsequent Bonferroni adjustment for multiple comparisons. The role of self-reported ethnicity will be evaluated with an interaction term; analyses will also be repeated within each self-reported ethnic group, and in the aggregate of groups where minor allele frequencies are comparable. As these experiments involve validation of previous hypotheses, nominal *P* values below 0.05 will be considered statistically significant.

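### Aims 1 and 2 ask about response to a drug, but the primary endpoints compare on-drug levels by genotype and make no use of the pre-drug Day 1 values

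*Protocol*

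**What the plan says.** The Specific Aims are framed as response. Aim 1 is "To examine the acute response to a sulfonylurea challenge (glipizide 5 mg orally) in subjects at risk of diabetes or with early diabetes", by genotype. Aim 2 is "To examine the acute response to short-term metformin treatment on the insulin sensitivity index in the same group", and its hypothesis is "We hypothesize that subjects with a subset of variants will have a diminished improvement in insulin sensitivity compared to non-carriers".

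VI.1 then fixes the primary endpoints. For Aim 1: "Trough glucose and peak insulin levels will be compared by genotype". For Aim 2, the reciprocal of HOMA insulin resistance "will be calculated as 22.5/[fasting insulin x (fasting glucose/18.01)], and compared by genotype". The Aim 1 secondary endpoints are trapezoidal areas under the curve, not stated to be incremental over time 0, and 2-hour values.

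VI.2 says of the outcome variables: "They will be adjusted for age, gender and BMI". The residuals are then compared between the two homozygous groups by t test. No pre-drug value is listed.

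V.2 shows that such values exist. Before glipizide on Day 1, "baseline (time 0) serum insulin, metabolomic profiling, C peptide and glucose will be obtained". This precedes metformin as well, which starts on the evening of Day 6 (V.4).

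I.3.b reports that KCNJ11 lysine carriers with IGT "had reduced insulin secretion at baseline". I.3.c reports the same direction in normoglycemic K carriers, and a lower insulinogenic index in TCF7L2 TT homozygotes.

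**The concern.** A level measured on drug is the sum of where the subject started and what the drug did. Comparing that level by genotype mixes the two. In most trials randomisation balances the starting level. Here the groups are defined by genotype and are not randomised, and the plan gives both drugs to every subject who passes the safety checks, so there is no untreated group to show what the level would have been. The Day 1 fasting sample is the only untreated reference.

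The error can run both ways. A genotype that only shifts the untreated level could be reported as changing drug response. A genuine response difference could also be hidden by an opposite difference at baseline. Either would misdirect the outcomes trial for which this pilot is meant to lay the ground.

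**Working it through.** **1. Question against endpoint.** Aim 1 asks for response to glipizide; the endpoint is a post-dose extreme. Aim 2 asks for improvement in insulin sensitivity, which is a within-person change; the endpoint is one value of the index. All the ingredients of a pre-drug index (fasting insulin and glucose) are collected on Day 1, yet no primary endpoint or model uses them.

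**2. Group sizes.** From VI.3, N = 750 and a K allele frequency of 0.35 under Hardy-Weinberg equilibrium: KK = 0.35² × 750 = 92; EE = 0.65² × 750 = 317. The standard error of a mean difference, in SD units, is √(1/92 + 1/317) = 0.1184.

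**3. The plan's own figure.** VI.3 gives 94% one-sided power for a 20% difference in peak insulin. It cannot be rebuilt because no SD is stated. Solved backwards: (1.555 + 1.645) × 0.1184 = 0.379 SD, so the implied SD is 20%/0.379 = 53% of the mean. A level comparison has the same power whether the difference arose before or after the dose. So if the whole 20% difference were present before dosing and carried through unchanged (an assumption), the test would still be significant in 94% of trials.

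**4. Smaller pre-existing differences.** Let d be the untreated difference in SD units, with identical drug response. The test statistic is shifted by d/0.1184, and two-sided 5% rejection is Φ(shift − 1.96) + Φ(−shift − 1.96). The values of d are assumptions; the documents give none.

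| d (assumed) | shift | rejection |
|---|---|---|
| 0.1 SD | 0.84 | 14% (0.135) |
| 0.2 SD | 1.69 | 39% (0.393) |

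**5. Which use of time 0 removes the bias.** Let r be the pre/post correlation (assumed), with equal SDs.

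- Change from time 0: the pre-existing difference cancels, so rejection is 5%.
- Time 0 as a covariate: the slope is r, so d(1 − r) remains and the residual SD is √(1 − r²). The shift becomes 1.69 × √[(1 − r)/(1 + r)]. For d = 0.2, r = 0.5 gives 0.98 and 16% rejection; r = 0.7 gives 0.71 and 11%.

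Simulation of the 0.379 SD scenario (4,000 runs per setting, one-sided 5%, no difference in drug response) agrees:

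| r | level | change | covariate |
|---|---|---|---|
| 0.5 | 94% | 5% | 57% |
| 0.7 | 94% | 5% | 36% |
| 0.9 | 94% | 5% | 18% |

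**6. Masking.** With a response difference of 0.379 SD and an equal and opposite baseline difference, the level comparison is significant in about 5% of trials, and change from time 0 in 94% or more.

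**7. Price in precision.** With no baseline difference, change has variance 2(1 − r) relative to the level. The 94% stays 94% at r = 0.5 and rises to 99% at 0.7. Below 0.5 it falls: at r = 0.3, 3.20/√1.4 = 2.70 and Φ(2.70 − 1.645) = 86%.

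**The case against.** **The Aim 2 text is silent rather than wrong.** VI.1 names no visit for the index, and the aim itself speaks of improvement, so one could say that the derivation is left open. That is fair as far as it goes. But the formula defines a single value, that value is what is compared, and the covariates are listed without a pre-drug term. On either reading the text does not deliver the change that the hypothesis needs.

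**A reader might infer that on-drug sensitivity must differ by genotype in Aim 2.** The documents do not support that. The untreated differences in I.3.b and I.3.c concern insulin secretion. Neither section reports an untreated difference in fasting HOMA sensitivity by E23K; the sensitivity result in I.3.c was obtained one year after intervention. For Aim 2 the bias is a possibility, not an expectation.

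**For Aim 1, part of the documented difference is seen after an oral glucose load.** Fasting time-0 values may capture only some of it. This stands as a limit: change from time 0 removes the starting level, not a secretory difference that appears only on stimulation.

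**A reader might infer a power gain, with the stated 73% for Aim 2 rising to 84–95% at correlations of 0.5 to 0.7.** This should not be claimed. The 73% conflicts with its own sentence: more than 90% one-sided implies at least Φ(1.282 + 1.645 − 1.960) = 83% two-sided. Only correlation beyond age, gender and BMI would count, and the gain presumes no baseline difference between genotypes.

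**This is a pilot and no data are lost.** That is true, since the Day 1 samples are drawn anyway. It makes the repair cheap, but does not make the planned comparison answer the question.

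**Conclusion.** The point holds. The primary endpoints for Aims 1 and 2, with the covariates in VI.2, cannot separate a drug-response difference from a genotype difference already present before the drug. The protocol's own preliminary data support the risk directly for Aim 1. For Aim 2 the bias is conditional on an untreated difference in fasting insulin or glucose, but the mismatch between hypothesis and endpoint does not depend on it.

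The sizes are illustrative: about 14% or 39% false positives for an assumed pre-existing difference of 0.1 or 0.2 SD at 92 against 317 subjects. They rest on Hardy-Weinberg counts at N = 750, equal SDs and a drug effect that is the same shift in both groups on the scale analysed. That last assumption also underlies the 5% for change from time 0, so the scale (log where the variable is log-transformed) should be fixed in advance. Covariate adjustment alone is not a sufficient remedy, because it under-corrects when non-randomised groups truly differ at baseline.

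**What to change.** In VI.1 and VI.2:

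- Aim 1 primaries: change from Day 1 time 0 to trough glucose, and from time 0 to peak insulin, on the log scale where the variable is log-transformed.
- Aim 2 primary: log insulin sensitivity index on Day 8 minus the log index at Day 1 time 0.
- Compare both by genotype with the existing covariates.
- Report models with the time-0 value as a covariate as sensitivity analyses, and raw on-drug levels as descriptive.
- Restate the power in VI.3 on the change scale, with the SD and pre/post correlation assumed.

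The cost is wording: no new samples or visits. Subjects without a usable time-0 sample drop out of the analysis. That should be few, since V.2 has baseline blood drawn even when the glipizide challenge does not go ahead. Change loses some precision if the pre/post correlation is below 0.5. The Aim 2 secondary endpoint, the insulinogenic index after metformin, cannot be repaired this way because Day 1 has no OGTT. It should be described as an on-drug level, not as a response.
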